## Abstract

Depression and suicide are leading public health problems requiring complex multilevel interventions. This study protocol details the COMBINA trial, which expands the evidence-based European Alliance Against Depression (EAAD) Community-Based 4-level intervention to also focus on improving wellbeing and tailored to five groups with increased vulnerability to depression: young people, older people, migrants/refugees, the long-term unemployed, and people with an existing mental health condition. In this prospective, non-randomised controlled trial, the COMBINA project will be newly implemented during a 24-month period, from late 2024 to late 2026, in five regions in Albania, Estonia, Greece, Ireland, and Spain. These regions will be compared to five control regions in the same countries, chosen to reflect a similar context, size, and sociodemographic characteristics. Main outcomes are a comparison between the intervention and control regions in the rates of deaths by suicide and hospitalisations for suicide attempts and the levels of wellbeing, depressive symptoms, anxiety symptoms, depression-related stigma, and willingness to seek psychological help in the general population. A process evaluation and economic evaluation will also be conducted. This intervention protocol also details the steps taken to promote successful implementation across a range of different cultural and regional contexts, with challenges including different existing mental health resources and differing capacities for the population to use digital tools. The COMBINA project includes co-creation, whereby materials and implementation strategy were designed with people from the vulnerable groups. The trial is funded by the European Union (grant agreement no. 101080651 and carried out according to the Declaration of Helsinki. Ethical approval has been obtained in all participating countries. The results will be published in peer-reviewed academic journals, presented at scientific meetings and disseminated through COMBINA stakeholders, with participation from the co-creators. This trial protocol (version 1.1, 24/10/2024) was registered in the ISRCTN registry (ISRCTN10521127) on 14/11/2025 (https://www.isrctn.com/ISRCTN10521127).

## Introduction

Depression remains a leading cause of disability worldwide, and its burden continues to rise in high-income regions. Major depressive disorder affects approximately 6.5-6.9% of the population each year [1,2] and poses substantial challenges for health systems [3,4], leading to a high clinical as well as economic burden of disease [5]. Furthermore, depressive disorders account for approximately 50%–60% of suicide deaths globally, making depression the most common underlying mental disorder associated with suicide [6–8]. Each year, an estimated 1,000,000 suicides occur worldwide [9], while attempted suicides are estimated to be about 20 times higher [10].

Suicide prevention is a public health issue driven by social determinants and individual and other risk factors [11], meaning it needs to be tackled at a community level, requiring action at different levels across the community [12,13]. A recent systematic review, which synthesised 47 studies published between 2010 and 2020, identified the European Alliance Against Depression (EAAD)’s community-based 4-level intervention as the most promising community-based intervention in terms of preventing suicide [14]. The EAAD intervention includes activities at four levels: 1) Primary health care, 2) General population, 3) Community facilitators, and 4) Patients and their relatives [15], and has been considered as a best practice intervention by the World Health Organisation and European Commission [10,16]. Since 2008, the concept has been implemented in more than 120 regions in 15 countries within Europe and beyond [17,18].

Despite growing evidence for the effectiveness of multi-level community interventions such as the EAAD model, their systematic implementation and long-term sustainability remain limited across Europe. Challenges to effective translation of evidence-based mental health interventions include insufficient adaptation to local contexts [19,20], limited engagement of vulnerable populations [21,22], and fragmentation between health and community sectors [23–26].

Within this context, the COMBINA study builds on the EAAD’s evidence-based 4-level approach by tailoring it to vulnerable groups and providing flexibility for implementation across different contexts. The 4-level intervention is adapted to meet the specific needs of five vulnerable groups who are often underserved by conventional mental health services: young people, older people, long-term unemployed, migrants and refugees, and people with current or past mental disorders. These vulnerable groups were chosen due to the risk of being underserved by existing mental health services. In terms of young people, the peak age of onset for mental disorders is 14.5 years old [27], yet the majority of young people do not seek professional help for mental health problems [28], and only approximately one third of adolescents with mental disorders receive treatment [29]. Conversely, older people have different specific needs, such as family-centred care [30], and are at risk of depression due to unmet healthcare needs [31]. Meanwhile, being unemployed is associated with higher rates of depression [32], and is also a risk factor for worse outcomes in depression [33] and for suicide [34]. Similarly, refugees and displaced people are at greater risk of a range of mental health conditions [35–37]. In voluntary migrants, a review showed consistent evidence for deterioration of mental health over time [38] and a lower sense of belonging in migrants is linked to increased anxiety and depression [39]. Finally, those with depression are at greater risk during societal change [40] and are likely to be undertreated [41], with a recent review finding only between 9% and 35% of people in Europe receive even minimal treatment for depression, depending on the country [42].

The intervention will be trialled across five regions within Albania, Estonia, Greece, Ireland, and Spain. These regions have diverse contexts and mental healthcare systems, requiring adaptation not only to vulnerable groups but to a range of new environments. The COMBINA project is also innovative in broadening the focus of the EAAD community-based 4-level intervention to improve wellbeing by including a focus on subclinical symptoms of anxiety and depression. Improved wellbeing has been shown to be a protective factor for depression [43,44], and psychological interventions for depressive symptoms not meeting clinical significance can improve them and prevent an episode of a depressive disorder [45,46]

The COMBINA trial, which forms part of the “MENTBEST: Protecting mental health in times of change” study funded by the European Union, will apply EAAD’s synergistic, multilevel, multicomponent community intervention, using a controlled non-randomized prospective design. The intervention will be implemented in five European regions. Each region will be paired with a comparable control region where no intervention activities will take place. The overall aims are to promote wellbeing and reduce depressive symptoms, suicide attempts, and the number of deaths by suicide, in the general population and among the five identified vulnerable groups. Furthermore, the intervention aims to reduce depression-related stigma and improve attitudes towards help-seeking for mental disorders.

## Methods

Although the study is not a randomised controlled trial, the evaluation design described in this manuscript is written in line with the StaRI reporting guidelines [47] and the SPIRIT checklist for trial protocols has been filled in, with items exclusively for randomised controlled trials marked as not applicable, and can be seen in Supporting Information S1 File.

### Study aims and design

A SPIRIT schedule of enrolment, interventions, and assessment can be seen in Fig 1, adapted to the multi-level non-randomised nature of our study. More detail regarding the overview of the study can also be seen in Fig 2. The study has three primary aims:

**Fig 1 pone.0352598.g001:**
[figure not shown]
SPIRIT Participant timeline: Schedule of enrolment, interventions, and assessments.

**Fig 2 pone.0352598.g002:**
[figure not shown]
Protocol Overview. Cross-country study protocol flowchart illustrating the main steps: region selection (control regions are shown within boxes with dashed borders), implementation of the 4-level intervention, evaluation components, and timeline (0–24 months; Mth = months).

Process evaluation: to comprehensively investigate the context-related implementation process of the intervention, including fidelity, reach, adoption, acceptability, and contextual facilitators and barriers across diverse European settings (Albania, Estonia, Greece, Ireland, and Spain).Outcome evaluation: To examine whether the expanded four-level intervention achieves its intended outcomes through a controlled, cross-country design. The evaluation will focus on clinical outcomes (e.g., reductions in suicidal behaviour and depressive symptoms) and non-clinical outcomes (e.g., improvements in wellbeing, self-reported mental health, and attitudes toward depression and help-seeking). Additionally, pre-post assessments without a control group will be included as well.Economic evaluation: to determine the cost-effectiveness of the intervention, expressed as the observed incremental cost per unit of outcome gained: cost per death by suicide avoided, per suicide attempt avoided and per percentage point improvement in selected clinical and subclinical outcomes derived from the population surveys conducted in each site.

The effectiveness of the expanded community-based 4-level intervention will be evaluated through a prospective controlled cross-country design across five European countries – Albania, Estonia, Greece, Ireland, and Spain. In each country, one intervention region and one comparable control region will be selected to allow for between-group comparisons. Primary clinical outcomes will be collected in both intervention and control regions to assess changes in depressive symptoms, suicidal behaviour, and wellbeing. Additionally, intermediate clinical and service-related outcomes will be collected in the intervention regions only to explore mechanisms of change and evaluate the broader system-level impact of the intervention.

The process evaluation will be conducted in both the intervention and control regions, using a mixed-methods approach that integrates both quantitative and qualitative data collection measures.

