### Implementation process

#### Data collection.

Participant recruitment and data collection for this trial began 24/09/2024 and will be completed by 31/12/2027. Participant recruitment will be completed by 31/01/2027, and data collection will be completed by 31/12/2027. Results will be provided by 31/03/2028. Recruitment began at different timepoints in the countries depending on when ethical approval was received. Recruitment began on 24/09/2024 in Greece, on 01/10/2024 in Estonia, on 07/10/2024 in Albania, on 12/11/2024 in Spain, and on 27/11/2024 in Ireland. The completion point for data collection is the same in all countries: 31/01/2027. Quantitative and qualitative data will be collected to support the outcome, process, and economic evaluations of the COMBINA intervention, as illustrated in Table 3. Please see Fig 4 for an overview of the timeline of the implementation process and different aspects of data collection. To guide the selection of indicators and measures, an Implementation Research Logic Model was developed for the EAAD community-based 4-level intervention and its implementation [75]. This model provides a detailed and comprehensive mapping of: determinants influencing implementation, implementation strategies employed, mechanisms of action, implementation outcomes, and clinical outcomes. An overview of this logic model is available in Supporting Information S2 File.

**Table 3 pone.0352598.t003:** Overview of indicators used for the data collection.

Indicator category	Indicator	Data source	Timing of data collection	Where collected
Outcome	Rates of completed suicide	Official statistics from responsible authorities in intervention and control sites	Retrospective and prospective rates from the period 2018–2026	Intervention and control regions
	Rates of hospitalisations due to suicide attempts	Medical records from hospitals in intervention and control sites	Rates from the period 2018–2026	Intervention and control regions
	Knowledge and attitudes related to depression, help-seeking, wellbeing, and symptoms of depression/anxiety	Validated surveys^a-d^ among general population in intervention and control sites	Before and 24 months after implementation	Intervention and control regions
	Competencies of professionals (Level 1 and Level 3 trainings)	Online validated survey^e,f^	Before and immediately after each training session	Intervention regions only (not applicable to control regions)

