### Outcome evaluation

The outcome evaluation will primarily focus on **changes in attempted suicide rates**, operationalised as hospitalisations for intentional self-harm, comparing intervention and control regions over the 2-year implementation period. Monthly hospitalisation data for intentional self-harm will be retrospectively extracted from hospital records covering September 2019 to August 2026, from hospitals serving residents of the intervention and control regions and agreeing to provide data. **Suicides**, including deaths of undetermined intent, will be analysed as a **key secondary outcome**. Annual suicide mortality data will be obtained from national statistical offices for the years 2018–2026 and expressed per 100,000 population by gender.

Other secondary outcomes include changes in public knowledge and attitudes toward depression and its treatment, and mental wellbeing. These will be assessed through general population surveys conducted in both intervention and control regions at baseline and 24-month follow-up, with samples of 500 residents per region. The chosen sample size is consistent with earlier large-scale evaluations of the EAAD multi-level intervention [76], which successfully used regional samples of approximately 500 respondents to detect meaningful changes in depression stigma, attitudes toward help-seeking, and awareness of campaign activities across intervention and control regions. Replicating this sampling approach ensures sufficient power to detect small-to-moderate changes in our outcomes. The samples are stratified by age and gender, following predefined quota for the target population, and recruited through a mix of face-to-face interviews, telephone interviews, and online surveys. Surveys were carried out by external accredited market research agencies, to improve methodological robustness and reduce selection bias. The survey includes sociodemographic and health-related questions, and four validated scales. Below, the English language versions of the scales are described. Validated translations were used for Albanian, Estonian, Greek, and Spanish, and where no validated scale was available, a back translation process was used.

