### Economic evaluation

The economic evaluation will use a cost-consequence analysis from both healthcare payer and societal perspectives. Costs considered include:

**Direct implementation costs** estimated using a micro-costing approach [79], which involves detailed tracking of resource use and unit costs.**Healthcare costs** related to suicide (attempts), based on published literature and/or hospital data.**Other societal or private costs** related to suicide (attempts), based on published literature and expert opinion (e.g., informal care).**Productivity losses**, calculated per full day of inpatient stay following a suicide attempt, its follow-up period or productivity loss due to premature mortality in case of a successful attempt.

Where feasible, country-specific cost estimates will be derived using local data sources. Outcomes linked to the cost estimates in incremental cost-effectiveness ratios include hospitalisations due to suicide attempts (primary economic outcome), deaths by suicide, and changes in public knowledge, attitudes, and mental wellbeing, as measured through the general population survey. Reporting will occur conform the CHEERS guidelines [80].

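### Study aims and design, and more loosely the Abstract, contradict Outcome evaluation on which outcomes are primary

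*Protocol article*

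**What the plan says.** Four places in the protocol article bear on the rank of the outcomes.

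- **Outcome evaluation** gives a hierarchy. The primary focus is the attempted suicide rate, "operationalised as hospitalisations for intentional self-harm, comparing intervention and control regions over the 2-year implementation period". Suicides, "including deaths of undetermined intent, will be analysed as a" key secondary outcome, come next. Then: "Other secondary outcomes include changes in public knowledge and attitudes toward depression and its treatment, and mental wellbeing". The last group is measured by population surveys "with samples of 500 residents per region", which also carry the PHQ-4 for depression and anxiety.
- **Economic evaluation** takes the same lead outcome: "hospitalisations due to suicide attempts (primary economic outcome").
- **Study aims and design** (the text following the Fig 2 caption) says: "Primary clinical outcomes will be collected in both intervention and control regions to assess changes in depressive symptoms, suicidal behaviour, and wellbeing". Earlier in the same section, the outcome evaluation aim gives wellbeing as an example of a non-clinical outcome.
- **Abstract**: "Main outcomes are a comparison between the intervention and control regions in the rates of deaths by suicide and hospitalisations for suicide attempts". The sentence goes on to five survey measures: wellbeing, depressive symptoms, anxiety symptoms, stigma and help-seeking. None is ranked.

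Table 3 does not settle the matter. It lists "Rates of hospitalisations due to suicide attempts" beside suicide rates, the survey measures and the training and online-tool measures under a single outcome category.

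**The concern.** A primary outcome must have the same rank wherever it is described, because that rank decides which result carries the conclusion on effectiveness. Here a report could cite Study aims and design to present wellbeing or depressive symptoms as primary. It could equally cite Outcome evaluation to present hospitalised self-harm as primary. If the two disagreed in direction or significance, the article would support either account.

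Three features of this trial sharpen the point.

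- Registration is dated 14/11/2025 and recruitment began on 24/09/2024, so registration came more than a year after the start. A consistent hierarchy in the protocol itself is therefore a more important safeguard than usual.
- The hospital outcome depends on hospitals that agree to provide data, and the Discussion acknowledges that the availability and quality of suicide and attempt data vary. If those data prove thin, attention may shift to the surveys.
- The survey outcomes are the only ones for which the article gives a sample-size rationale.

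**Working it through.** The article gives no alpha, power or effect size tied to a primary outcome, so there is no stated figure to reproduce. The check is a comparison of text, followed by an illustrative calculation.

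**Step 1. Rank of each outcome by section**

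| Outcome | Abstract | Study aims and design | Outcome evaluation |
|---|---|---|---|
| Hospitalised self-harm / attempts | main | primary clinical (as suicidal behaviour) | primary focus |
| Suicide deaths | main | primary clinical, if suicidal behaviour includes deaths | key secondary |
| Wellbeing (WHO-5) | main | primary clinical, and elsewhere in the section non-clinical | other secondary |
| Depressive symptoms (PHQ-4) | main | primary clinical | not named in the ranking sentences; part of the survey used for other secondary outcomes |
| Anxiety symptoms (PHQ-4) | main | not listed | same as depressive symptoms |
| Stigma (DSS) | main | not listed | other secondary (attitudes) |
| Help-seeking (ATSPPH-SF) | main | not listed | other secondary (attitudes) |

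Reading across:

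- Wellbeing is a direct contradiction: primary in one section, secondary in another.
- Suicide deaths conflict on the natural reading of suicidal behaviour.
- Depressive symptoms are primary in one section and have no explicit rank in the other, where they appear only through a secondary-outcome survey.
- Only hospitalised self-harm is at the top in all three columns.

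**Step 2. Number of top-level outcomes**

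- Outcome evaluation: 1.
- Study aims and design: 3 domains, or 4 outcomes if suicidal behaviour is split into attempts and deaths.
- Abstract: 2 rates + 5 survey measures = 7, labelled main and not primary.

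**Step 3. What the count could mean (illustration)**

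Assumptions, none of them stated in the article: each outcome is tested at 5%, the tests are independent, there is no correction, and success is claimed if any one is significant. The chance of at least one false positive among k outcomes is 1 − 0.95^k.

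- k = 1: 1 − 0.95 = 0.050
- k = 3: 1 − 0.8574 = 0.143
- k = 4: 1 − 0.8145 = 0.186
- k = 7: 1 − 0.6983 = 0.302

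The survey scales are answered by the same respondents, so positive correlation is likely and would lower these figures.

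**The case against.** The strongest reply is that a hierarchy already exists. Outcome evaluation is the dedicated section, it names one primary focus and ranks the rest, and Economic evaluation agrees. That stands. A reader might infer that the trial has no fixed primary endpoint, but the document does not support that: it has one that is not stated consistently.

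A second reply is that the Abstract says main, not primary, and may simply summarise what is compared between regions. That also stands. A reader might count three rival sets of primary outcomes, but only two sections use the language of primacy.

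A third reply is that in Study aims and design the next sentence contrasts these outcomes with intermediate ones collected in intervention regions only, so primary may there mean compared between regions. This is plausible, and the clinical label on wellbeing does suggest loose drafting. It softens the conflict without removing it, because primary outcome has an established meaning in a trial protocol and nothing in the section tells the reader to set it aside.

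A fourth reply is that success criteria and multiplicity rules commonly sit in an analysis plan, which is not shown. That is correct, and their absence is not part of this point. A reader might infer that the trial may claim success on any of several outcomes, but no such rule is written. The rank of outcomes is different: the article states it, and does so in conflicting ways.

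Finally, although registration was late, it precedes both the August 2026 end of the hospital extraction window and the 24-month surveys. Nothing in the article shows that endpoints were chosen after results were seen.

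**Conclusion.** The contradiction is on the face of the article and should be corrected. Study aims and design gives primary status to wellbeing, depressive symptoms and, on its natural reading, suicide deaths. Outcome evaluation ranks wellbeing and suicide deaths as secondary and gives depressive symptoms no explicit rank. The Abstract's unranked list of seven matches neither.

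The consequence is that a survey result could be labelled primary, with textual support, while the hospital outcome is null. The figures of 14%, 19% and 30% show how much the count of outcomes could matter under the stated assumptions. They do not estimate this trial's error rate, and the conclusion does not depend on them.

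Two further inferences are not supported. The limitations section says that the low frequency of suicide deaths makes a statistical link challenging. It does not say that one is impossible, and the remark fits a key secondary rank. The registry entry was not available, so whether it agrees with either section is unknown.

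**What to change.** Adopt the Outcome evaluation hierarchy everywhere:

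1. In Study aims and design, replace *Primary clinical outcomes* with *Outcomes compared between regions*, and remove the conflict over whether wellbeing is clinical or non-clinical.
2. In the Abstract, replace the unranked list with the ranked one: hospitalisations for intentional self-harm as primary; suicides, including undetermined intent, as key secondary; the survey scales as other secondary.
3. In Outcome evaluation, state the rank of the PHQ-4 explicitly, as other secondary alongside WHO-5, DSS and ATSPPH-SF.
4. State that the main conclusion on effectiveness rests on the primary outcome.
5. Check that the registry entry gives the same hierarchy.

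All of this should be done before outcome data are analysed. The cost is rewording in three sections and one registry check; no data collection or design element changes. The real downside is that a favourable survey result could no longer be called a primary result.
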